#### Psychological distress

*Distress levels* are measured using the Distress Thermometer. The Distress Thermometer (DT) is a one-item, 11-point Likert scale represented on a visual graphic of a thermometer that ranges from 0 (no distress) to 10 (extreme distress). The adult/caregiver version has 15 accompanying checkboxes for areas of distress [36] while the pediatric version has 38 checkboxes for areas of distress [37]. The DT is reported to have sound psychometric properties [36, 37]. For the purpose of this study, scores below 4 represents low distress, 4–6 represents moderate distress, and ≥ 7 represents high distress. This measure is administered monthly.

#### Quality of life (QOL)

*QOL of child/teen* (based on self-report and caregiver report) are measured using the PedsQL 4.0–generic and PedsQL 3.0–cancer. PedsQL 4.0 is a 23-item scale that provides a total and four subscale scores (physical, social, emotional, and school functioning) [38]. It has adequate test-retest reliability and validity. PedsQL 3.0 is a 24-item cancer-specific scale with a total and eight subscales including: pain, nausea, procedure, and treatment anxiety [39]. Raw scores in both scales are linearly transformed to a 0 to 100 scale (higher scores reflect better QOL). The PedsQL-3.0 has adequate test-retest reliability and validity [39]. Scores below 69 are considered poor QOL [40].

*Caregiver QOL* is assessed using the Caregiver Quality of Life Cancer Scale*,* a 35-item questionnaire that assesses QOL globally and across four domains: burden, positive adaptation, disruption, and financial; lower scores indicate better quality of life [41]. The validity and reliability of this measure is adequate.

#### Social relations and coping

*Socio-emotional support* will be measured using the PROMIS. The PROMIS-emotional support is a 7-item (pediatric) and 6-item (adult) measure with a 5-point Likert scale. T scores below 30 represents poor peer relationships, 30–40 represent fair peer relationships, 40–60 represent good peer relationships, and ≥ 60 represents excellent peer relationships.

*Peer relationship support* is measured using the PROMIS. The PROMIS-peer relationship is an 8-item (pediatric) measure with a 5-point Likert scale. T scores below 30 represent poor peer relationships, 30–40 represents fair peer relationships, 40–60 represents good peer relationships, and ≥ 60 represents excellent peer relationships.

*Coping* with cancer diagnosis is measured using the Responses to Stress Questionnaire-Cancer version (RSQ-PC). The RSQ-PC is a measure of coping and involuntary stress responses. The factor structure of the RSQ has been supported in confirmatory factor analysis studies with children and adolescents from a wide range of ethnic and cultural backgrounds coping with a variety of stressors [42]. The coping scales include primary control coping (i.e., problem solving, emotional modulation, emotional expression), secondary control coping (i.e., acceptance, cognitive restructuring, positive thinking, distraction), and disengagement coping (i.e., avoidance, denial, wishful thinking). Using the standard method for scoring the RSQ, and to control for response bias and individual differences in base rates of item endorsement, proportion scores are calculated by dividing the total score for each factor by the total score for the RSQ [43].

#### Physical measures

*Sleep quality* is assessed using the Pittsburgh Sleep Quality Index (PSQI). The PSQI is a self-rated questionnaire which assesses sleep quality and disturbances over a 1-month time interval. Nineteen individual items generate seven “component” scores including subjective sleep quality and sleep duration. The sum of scores for these seven components yields one global score; scores greater than 5 indicates poor sleep quality. The PSQI is reported to have acceptable psychometric properties [44].

*Fatigue symptomatology* is measured using the PROMIS. The PROMIS-fatigue is a 10-item (pediatric) and 6-item (adult) measure with a 5-point Likert scale. The items are added to provide a raw score which is then converted to a T-score. For the purpose of this study, a T score below 55 represents low symptoms, 55–64.9 represents moderate symptoms, and ≥ 65 represents high symptoms.

*Pain-related quality of life* is measured via the pain subscale of the PedsQL (see above).

### Data analysis

#### Quantitative data analysis

Preliminary analyses will include descriptive statistics for key study variables of feasibility. First, frequencies and percentage rates will be collected for measures of feasibility such as recruitment, retention, and withdrawal. Consistent with previous research [33, 45, 46], the intervention will be feasible if at least 50% of newly diagnosed families are recruited to the study, 80% of the targeted sample size (n = 40) is recruited, at least 70% of the sample is retained, and fewer than 30% of participants withdraw from the study. The intervention will be acceptable if at least 75% of the IG rate the intervention as ‘pretty much’ or ‘very much’ acceptable.

Preliminary t tests on the secondary and exploratory outcome measures will be conducted to determine which outcome measures should be further examined in the larger multi-site trial.

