### Randomization

Upon completion of baseline measures, participants are randomly allocated at a 1:1 ratio to either the IG or CG. Using computer-generated numbers, the randomization is managed by the research coordinator for the project. The study coordinator maintains a double password-protected file with details of randomized allocation and reveals the randomization outcome to PSN after dyads complete consent procedures.

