### Sample size

As recommended for pilot RCT [33], enrolling 36–40 consenting patients-caregiver dyads, 18–20 in each group, will be acceptable to achieve the study objectives (see Fig. 2, participant flow chart).

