**Fig. 4 Fig4:**
[figure not shown]
Example of Monthly Distress Thermometer Communication for a Fictional Patient

All participants complete the assessment measures at baseline and 12 months and participants in the IG group also complete the screening measure monthly (see below). At the 12-month follow-up, based on their preference, participants will either have survey packets mailed to them with pre-stamped envelopes to return completed surveys, or emailed to them via a secured link to REDCap. In the IG, personalized results from the psychosocial risk assessment and anxiety and depression assessment at baseline, and monthly distress screenings, are used to tailor resource recommendations for the youth and caregiver, which are shared with them and the youth’s treating team. The validated instruments are described below. Additionally, at 12 months, after completing the quantitative measures, the IG group participants complete a brief questionnaire of intervention acceptability and are invited to engage in a short semi-structured interview (approximately 15 min; see Table 3) where they are asked to describe their overall experience of the study. This interview is conducted either in person or over the telephone, depending on participant preference and availability. Interview data are audio-recorded and transcribed verbatim. The time line for the IG and CG is presented in Fig. 2.

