### Feasibility and acceptability

Outcomes and endpoints for feasibility are measured by criteria of intervention acceptability; recruitment and retention; intervention satisfaction; and feasibility of completing outcome measures of intervention effectiveness.

Acceptability will be assessed using (a) estimates of recruitment, retention, and withdrawal rate; (b) estimates of completed assessment screenings, data collection procedures, and specific outcome measures; (c) in the intervention group, youth’ and parents’ perceptions of the acceptability of EPSI intervention, including their acceptability of monthly screening and feedback by the PSN, as well as their views about the intervention gathered during the end of intervention interview. Finally, (d) examination of treatment effects (e.g., effect sizes, variance measures/standard deviation) on secondary mental health and quality of life outcomes and exploratory variables will inform the selection of outcome measures for the future, definitive RCT.

*Intervention acceptability* is measured by participation in screening, assessment, and intervention activities (defined as treatment accepters when the participant completes all required measures and questionnaires). Recruitment and *retention* will be measured by (i) accrual and dropout rates; and (ii) proportion of completed questionnaires (defined as 100% when all measures completed at baseline and 12 months post-baseline). *Intervention satisfaction* will be measured by (i) comparing recruitment and retention between both groups; (ii) brief questionnaire completed by all caregivers and youth at the completion of study; and (iii) by the semi-structured interview completed by youth and caregivers who participate in the IG (Table 3). Finally, potential benefits of EPSI will be estimated comparing the secondary outcomes (mental health and quality of life) and exploratory outcomes (coping, social relationships, and physical functioning) in the IG and CG.

**Table 3 Tab3:** Semi-structured interview questions

1. **Thinking back to when you first agreed to participate in the study, what was it about the project that made you say “yes”?**	
2. **What was it like for you to participate in the study? (Tell us about your own experience?)**	
3. **What were your expectations about being in this study?**	
4. **How were your expectations met or not met? (Explain.)**	
5. **How did you find the experience with the Psychosocial Navigator?**	

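### The planned t tests on secondary and exploratory outcomes make no stated use of baseline as a covariate; adjusting each 12-month score for its own baseline would be more precise and would remove the effect of chance imbalance.

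*Protocol article*

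**What the plan says.** The Quantitative data analysis section gives one between-arm method for the secondary and exploratory outcomes: "Preliminary t tests on the secondary and exploratory outcome measures will be conducted". Their stated purpose is to pick the outcomes that the later, larger trial will study. The Feasibility and acceptability section gives the results a related use. There, "examination of treatment effects (e.g., effect sizes, variance measures/standard deviation) on secondary mental health and quality of life outcomes" and on the exploratory variables is to guide which outcomes the definitive RCT will measure, and "potential benefits of EPSI will be estimated comparing the secondary outcomes (mental health and quality of life) and exploratory outcomes" between the two arms. No baseline covariate, change score or repeated-measures model is named anywhere in the article.

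Baseline values are available. The Intervention section states: "All participants complete the assessment measures at baseline and 12 months". Table 2 marks both visits for every listed outcome except the satisfaction questionnaire. The Randomization section puts baseline first: "Upon completion of baseline measures, participants are randomly allocated at a 1:1 ratio to either the IG or CG". No stratification on baseline scores is described. The caregiver quality-of-life scale, described under Quality of life (QOL), has no row in Table 2, so its baseline assessment rests on the general statement in the Intervention section alone.

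On size, the Sample size section says "enrolling 36–40 consenting patients-caregiver dyads, 18–20 in each group, will be acceptable to achieve the study objectives". The feasibility criteria accept retention down to 70%.

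**The concern.** With 14 to 20 dyads per arm, the arms can easily differ at baseline by chance on any one scale. A t test on 12-month scores carries part of that difference into the effect size. A t test on change scores removes too much of it. Both give wider intervals than a model that estimates the baseline slope, unless r is very low or very high.

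At stake is the choice of outcomes for the definitive trial, because the t tests and effect sizes are what the article uses to make it. An outcome could be kept or dropped partly because of where the arms happened to start. The information needed to reduce that risk is already being collected.

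**Working it through.** The sample size is a pilot rule of thumb with no alpha, power, SD or effect size, so there is no figure of the plan's own to reproduce. The check compares the precision of three analyses.

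**Inputs from the article**
- 18–20 per arm (Sample size); 20 is used as the upper case.
- Lowest accepted retention 70% (Quantitative data analysis): 0.70 × 20 = 14 per arm.
- Baseline measured before 1:1 allocation (Randomization).
- Illustrative effect d = 0.60: caregiver depression in the targeted/clinical subgroup of the team's earlier trial (Background).

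**Assumptions, not in the article**
- Two-sided alpha of 0.05.
- r = 0.3, 0.5 or 0.7.
- Equal SD at both visits. All results are in units of that SD.

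**Chance baseline imbalance.** The SD of the between-arm difference is √(2/n).
- n = 20: √0.100 = 0.316; P(|difference| > 0.5) = 2[1 − Φ(0.5/0.316)] = 0.114.
- n = 14: √0.143 = 0.378; P(|difference| > 0.5) = 2[1 − Φ(0.5/0.378)] = 0.186.

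**Effect of a 0.5 SD imbalance on the estimate,** for r = 0.3/0.5/0.7:
- 12-month scores: r × 0.5 = +0.15/+0.25/+0.35 SD (under-corrected).
- Change scores: (r − 1) × 0.5 = −0.35/−0.25/−0.15 SD (over-corrected).

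**Variance factors relative to a 12-month t test**
- Change scores, 2(1 − r): 1.40/1.00/0.60.
- ANCOVA, 1 − r²: 0.91/0.75/0.51, before small-sample inflation for the estimated slope.
- Inflation, 1 + 1/(2n − 4): 1.028 at n = 20 and 1.042 at n = 14. ANCOVA factors become 0.94/0.77/0.52 and 0.95/0.78/0.53.

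**95% CI half-widths.** Each is t × √(variance factor) × √(2/n), with 2n − 2 degrees of freedom for the t tests and 2n − 3 for ANCOVA. Example at n = 14, r = 0.5: the 12-month t test gives 2.056 × 0.378 = 0.78, and ANCOVA gives 2.060 × √(0.75 × 1.042) × 0.378 = 0.69.

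| n per arm | r | t test, 12-month | t test, change | ANCOVA |
|---|---|---|---|---|
| 20 | 0.3 | 0.64 | 0.76 | 0.62 |
| 20 | 0.5 | 0.64 | 0.64 | 0.56 |
| 20 | 0.7 | 0.64 | 0.50 | 0.46 |
| 14 | 0.3 | 0.78 | 0.92 | 0.76 |
| 14 | 0.5 | 0.78 | 0.78 | 0.69 |
| 14 | 0.7 | 0.78 | 0.60 | 0.57 |

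**Where the advantage ends.** At n = 14, the inflated ANCOVA variance exceeds that of the 12-month t test only if 1.042(1 − r²) > 1, that is r below about 0.20. It exceeds that of the change-score t test only if 1.042(1 + r) > 2, that is r above about 0.92.

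**Power for d = 0.60** (noncentral t), 12-month t test against ANCOVA at r = 0.3/0.5/0.7:
- n = 20: 46% against 48%/56%/72%.
- n = 14: 33% against 35%/41%/55%.

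**The case against.** The strongest reply has four parts.

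**Change scores.** A reader might infer that the plan ignores baseline altogether. The text does not support that: it leaves the form of the score open, and a t test on change is possible. If change was meant, the gain from ANCOVA at r = 0.7 is 0.51 against 0.60, about 15% of the variance before inflation and not 49%, and imbalance pushes the estimate the other way. This stands as a limit on size. It does not rescue the plan, because the change-score variance is still larger at each r considered and the imbalance is over-corrected.

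**Validity.** A t test after randomisation is unbiased over repeated randomisations. That stands: the imbalance problem is conditional on this one small sample, so it would be wrong to call the planned test invalid.

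**Little depends on it.** The primary outcomes are feasibility and acceptability, judged by percentages; the t tests are labelled preliminary; and the article itself says a larger study is needed to examine effects. This stands and keeps the point modest. Yet the t tests still decide which outcomes go forward.

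**Detail for an analysis plan.** Covariates are often specified elsewhere. But the article names the method, so the point concerns what it states and not what it leaves out.

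**Conclusion.** The point holds as an inexpensive improvement to a stated method; it does not show an error that invalidates the analysis. Whichever score the t tests use, they are less precise than baseline adjustment for r between 0.3 and 0.7 and leave chance imbalance in the effect sizes. The benefit depends on an r that the article does not give: it is slight at 0.3 and substantial at 0.7, and the 14-per-arm figures describe the lowest accepted retention from 20 per arm, not the expected number.

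Two stronger readings should be avoided. One is that the definitive trial will be sized on an ANCOVA residual SD from this pilot; the article says only that effect sizes and SDs will inform outcome selection and, in general terms, that the pilot will inform planning. The other is that adjustment would make the outcome comparisons reliable; even at 20 per arm and r = 0.7, power for d = 0.60 is 72%, and at r = 0.5 the interval still extends 0.56 SD either side.

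**What to change.** In the Quantitative data analysis section, replace the t tests by a linear model for each 12-month score with group and that score's own baseline value as covariates, fitted separately for youth, caregiver and proxy scores. Report the adjusted difference with its 95% CI, the residual SD and the baseline to 12-month correlation. Add the caregiver quality-of-life scale to Table 2 with its assessment times, so that its baseline is on record.

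The cost is a change of wording and one degree of freedom per model. No new data, visits or participants are needed, and the feasibility and acceptability criteria stay as they are.

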#### Qualitative data analysis

After the semi-structured interviews are transcribed verbatim, they will be analyzed using inductive content analysis [47]. Analysis will consist of an iterative, open coding process where two primary coders will immerse themselves in approximately five transcripts. Recurring themes and relational patterns common across transcripts will be explored with the aid of charts and notes. The coders will meet regularly to compare notes and develop codes, keeping a paper trail throughout analysis [48]. Discrepancies will be resolved by consensus. Following open coding, categories, themes and subthemes will be grouped together to form a codebook with all codes defined. The primary coders will then code all transcripts using the codebook and MAXQDA software to facilitate the data analysis. Ten percent of interviews will be double coded by a third researcher to ensure acceptable (> 85%) inter-rater reliability.

#### Data management

Data is stored in line with HSC ethical procedures and requirements for storage and security of data. Participant questionnaires are identified with a numeric code and kept separate from all identifiable personal information such as names, addresses, and/or consent forms. Data quality will be checked using double data scoring and entry. Standard data management protocols are being followed. Only the study investigators and research assistants will have access to the study data. Ethics auditing procedures are determined by the institutional research ethics board.

#### Safety monitoring and reporting

Should a participant report risk to themselves or others, the research team will take all necessary steps to ensure the safety of the participant and others. All risks or safety issues will be reported to the Principal Investigator who will take any necessary further steps and provide ongoing clinical supervision to the research team as required. Additionally, data safety and monitoring board guidelines will be followed.

Debriefing sessions and clinical supervision with the Psychosocial Navigator (the research team member conducting the intervention) will take place regularly.

Any serious adverse events will be recorded and reported to the institutional ethics committee.

#### Ethical approval

The study received ethical approval from the Hospital for Sick Children Research Ethics Board on 2 November 2017 (REB # 1000056445). The trial will be conducted in accordance with the Ethics Approval at all times. The participants will be identified by a study-specific participant number in all databases. Any amendment to the protocol will be submitted to the research ethics board for approval.

#### Dissemination

The following knowledge translation activities will be conducted with the intention of advancing the field of screening for psychosocial risk and mental health in pediatric oncology: delivery of scientific rounds at the participating centers to disseminate relevant results for stakeholders in pediatric oncology as well as other pediatric chronic conditions; training workshops on the implementation of the intervention provincially and nationally; and participation in community presentations for parent organizations (e.g., Ontario Parents Advocating for Children with Cancer) and scientific presentations provincially (Pediatric Oncology Group of Ontario, POGO Symposium), nationally (Canadian Psycho-Oncology meetings, CAPO), and internationally (International Pediatric Oncology Association, SIOP).

## Discussion

A large barrier to implementation of screening programs is a lack of knowledge on *how* to follow-up from screening. This proposal describes a new intervention designed to bridge the gap between psychosocial screening and better health outcomes. By tailoring recommendations and resources to the assessment results initially and providing ongoing monthly feedback via the psychosocial navigator, we hope to capture potential changes in the psychosocial needs of the youth and the primary caregiver and improve their mental health outcomes. This proposal addresses the process of assessing feasibility and acceptability of the intervention and pilot testing of its possible benefits for the child and the primary caregiver using a randomized control trial. It is designed to meet recommended standards of care [14] and builds on extensive previous work in adult oncology [49] and preliminary findings in pediatric oncology [21, 26, 27].

Positive findings of feasibility and acceptability of the intervention will serve as the foundation for an RCT fully powered to test intervention effects. Broadly, this intervention may lead to earlier identification of families at-risk for poor quality of life and poor mental health and more efficient and precise triaging of resources based on measured risk, mental health, and distress in the youth with cancer and their family. This intervention has the potential to model a pathway forward on how to implement psychosocial screening in pediatric oncology. If successful, this intervention could then be expanded across other pediatric chronic conditions.

### Trial status

Recruitment began in November 2017. Thirty-eight dyads have been enrolled. We anticipate data collection will be completed by October 2020.

## Data Availability

Not applicable.

## Abbreviations

CSP: Communication Summary Profile
CG: Control group
DT: Distress thermometer
EPSI: Enhanced Psychosocial Screening Intervention
HCP: Healthcare provider
HSC: Hospital for Sick Children
IG: Intervention group
PAT: Psychosocial Assessment Tool
PPPHM: The Pediatric Preventive Psychosocial Health Conceptual Model
PROMIS: Patient-Reported Outcomes Measurement Information System
PSN: Psychosocial navigator
PSQI: Pittsburgh Sleep Quality Index
QOL: Quality of life
RCT: Randomized Controlled Trial
RSQ-PC: Response to Stress Questionnaire-Pediatric Cancer
